## Abstract

**Background:**

Obesity represents a growing threat to health with multiple negative impacts including urinary incontinence. Pelvic floor muscle training (PFMT) is the first line of treatment for urinary incontinence. Both surgical and conservative weight loss results in improvement of urinary incontinence reports in obese women and we hypothesize that a low-calorie diet in combination with PFMT would result in additional beneficial effects to urinary symptoms in women with UI compared would with weight loss alone.

**Objective:**

To assess the effect of a low-calorie diet plus PFMT protocol in obese women’s urinary incontinence reports.

**Methods:**

This is a protocol for a randomized controlled trial that will include obese women reporting UI and being able to contract their pelvic floor muscles. The participants will be randomly allocated in two groups: group 1 will participate in a 12-week protocol of low-calorie diet delivered by a multi-professional team at a tertiary hospital; group II will receive the same low-calorie diet protocol during 12 weeks and will additionally participate in 6 group sessions of supervised PFMT delivered by a physiotherapist. The primary outcome of the study is self-reported UI, and severity and impact of UI on women’s quality of life will be assessed by the ICIQ-SF score. The secondary outcomes will be adherence to the protocols assessed using a home diary, pelvic floor muscle function assessed by bidigital vaginal palpation and the modified Oxford grading scale, and women’s self-perception of their PFM contraction using a questionnaire. Satisfaction with treatments will be assessed using a visual analog scale. The statistical analysis will be performed by intention to treat and multivariate analysis of mixed effects will be used to compare outcomes. The complier average causal effects (CACE) method will be used to assess adherence. There is an urgent need for a high-quality RCT to investigate if the association of a low-calorie diet and PFMT can provide a larger effect in the improvement of urinary incontinence reports in women with obesity.

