## Methods

### Study design

We will conduct an assessor blind randomized, controlled, two-arm clinical trial to assess whether the combination of a low-calorie diet and PFMT will optimize the results obtained with diet therapy as a single intervention to decrease UI prevalence reports and severity in obese women (primary outcome). The secondary outcomes of this study are the impact of the protocol on PFM function, women’s self-perception of their PFM, adherence, and satisfaction with the treatment. This protocol will be reported according to the Protocol Items Standard: Recommendations for Intervention Trials checklist (SPIRIT) 2013: items recommended for a clinical trial protocol and related documents. It is a superiority trial.

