### Sample size calculation

The sample calculation was estimated considering a significance level of 5%, power of 20%, and difference of 4 points on the final score of the primary outcome, ICIQ-SF, between groups at the end of treatment [10]. The value of 4 points is equivalent to the minimum value for change in the questionnaire score. Thus, the sample will be composed of 22 participants.

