### Statistical analysis

Data will be de-identified, encoded, and stored in the database using the Excel Program. The software SPSS 22.0 will be used for the analysis of data. The description of quantitative variables will be expressed in mean, standard deviation, minimum value, median and maximum value. Qualitative variables will be described in absolute and relative values (%). A 95% confidence interval and 0.05 significance will be considered for all tests. Both per-protocol and intention-to-treat analyses will be performed.

A linear mixed-effect model will be used to analyze the ICIQ-SF score. In the reassessment, individuals’ values will be considered random effects, and the groups, the times, and the interaction between them will be regarded as fixed effects. In addition, the McNemar test will verify changes in categories variables before and after the intervention. Both per-protocol analysis [11–13] and an intention-to-treat analysis will be also conducted.

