### Assessment

#### Primary outcome measures

Self-report of urinary incontinence will be measured by question 3 of the ICIQ-SF. Women will be considered incontinent if they choose options 1, 2, 3, 4, or 5 of question 3. Women will be considered continent if they choose option 0 in question 3.

The severity and impact of urinary incontinence on women’s quality of life will be measured by the ICIQ-SF score.

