### Descriptive and control variables

The descriptive and control variables were divided into clinical variables (diabetes, hypertension, constipation, number of pregnancies, deliveries, cesarean sections, vaginal delivery; use of contraceptives and previous pelvic surgeries) sociodemographic variables (age, education, marital status, economic, smoking occupation, use of alcoholic beverages, physical exercise and use of caffeine) and anthropometric measures (height and body mass). The descriptive and control variables will be acquired from women’s self-report. The study variables are shown in Fig. 2 and Table 2.

**Table 2 Tab2:** Outcome measures and time points of the study assessment

Results	Instruments	Baseline	Post-intervention
Primary			
Urinary incontinence	“*International Consultation on Incontinence Questionnaire—Short Form*” score (ICIQ-SF)	√	√
Secondary			
Adherence of the participants	PFMT diary		√
PFM function	Bidigital vaginal palpation (MOS and Oxford modified)	√	√
Self perception	Safe Stimated based on the Modified Oxford Grading Scale	√	√
Satisfaction with treatment	Visual analog scale (VAS)		√
Subjective satisfaction	Participants will answer the following questions: are you satisfied with the treatment you received for UI? Would you do this treatment again? Would you recommend this treatment for other people? Would you pursue another treatment?		√
Identification of barriers to treatment	Participants will answer the following questions: Do you identify any barriers or difficulties in adhering to the treatment you received for urinary incontinence?		√
Diary about the adherence to PFMT			√

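### The primary outcome is stated inconsistently (self-reported UI, a pair of outcomes, or the ICIQ-SF score alone) and no success rule is given, so the superiority criterion is undefined

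*Protocol article*

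**What the plan says.** The protocol article describes the primary outcome in these places:

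- **Abstract, Methods:** "The primary outcome of the study is self-reported UI". The same sentence goes on to assign severity and quality-of-life impact to the ICIQ-SF score.
- **Study design:** the aim is "to decrease UI prevalence reports and severity in obese women (primary outcome"; the label covers prevalence and severity together. The trial is declared a superiority trial.
- **Primary outcome measures:** two measures. The first is binary: "Self-report of urinary incontinence will be measured by question 3 of the ICIQ-SF", with option 0 meaning continent and options 1 to 5 incontinent. The second is the total: "The severity and impact of urinary incontinence on women’s quality of life will be measured by the ICIQ-SF score".
- **Sample size calculation:** the score alone, sized on a "difference of 4 points on the final score of the primary outcome, ICIQ-SF, between groups at the end of treatment".
- **Table 2:** a single primary row, measured by the score of the "International Consultation on Incontinence Questionnaire—Short Form".

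Statistical analysis states: "A 95% confidence interval and 0.05 significance will be considered for all tests". It gives the score a linear mixed model with group, time and their interaction. For categorical variables it names only the McNemar test, before versus after the intervention.

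**The concern.** A yes/no continence status and a questionnaire total need different effect measures, tests and sample sizes. The article does not settle whether the trial succeeds on the first, the second, either or both. If the two disagree, nothing in the document says what the conclusion is, and the choice could be made after the data are seen.

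Two things add to this. The outcome that the abstract puts first is not the one that the sample size rests on. And the only test named for categorical outcomes compares women with themselves, so it does not address the randomised comparison.

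**Working it through.** **Inputs.** From the document: significance level 5%; 22 participants; a 4-point difference; 0.05 for all tests; all women report UI at entry (Inclusion criteria). Assumed, because the document does not give them: two-sided tests, 1:1 allocation (22/2 = 11 per arm), 80% power (the article's 20% read as the type II error), the correlation between the two test statistics, and the continence rates.

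**1. What 22 was sized for.** The figure cannot be reproduced, because no standard deviation is stated. Solved backwards with the normal formula, SD = 4 / [(1.960 + 0.842) × √(2/11)] = 3.35 points. The calculation contains no continence rate, so it can only be a calculation for the score.

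**2. Type I error under each possible success rule.**

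| Rule | Type I error |
|---|---|
| One outcome named as primary | 5% |
| Both required, two tests of exact 5% size | 0.25% (r = 0), 0.9% (r = 0.5), 2.2% (r = 0.8) |
| Either suffices, two tests of exact 5% size | 1 − 0.95² = 9.75% (r = 0), 9.1% (r = 0.5), 7.8% (r = 0.8) |
| Either suffices, Fisher's exact test for continence at 11 per arm | at most 5% + 1.7% = 6.7% |

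The values for r > 0 come from the bivariate normal distribution. Question 3 is an item of the score, so a positive correlation is to be expected and r = 0 is the extreme case.

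The last row uses the actual size of Fisher's test. Enumerating all outcomes at 11 per arm with equal true rates gives 0.2% (rate 10%), 1.0% (20%), 1.6% (40%) and 1.7% (50%, the maximum). Adding the two error rates bounds the total whatever the correlation.

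A simulation at 11 per arm with correlated outcomes gave 5.8% to 6.2% with Fisher's test and 7.8% to 9.1% with the chi-square test.

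**3. Power for the binary outcome.** Exact Fisher power, 11 per arm, assumed continence rates:

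- 10% v 40%: 19%
- 20% v 50%: 17%
- 20% v 60%: 32%

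**4. What McNemar can show.** All women are incontinent at entry, so status can change only towards continence. If 6 of 11 women in one arm become continent, the exact two-sided p is 2 × 0.5⁶ = 0.031. The same result in the other arm also gives 0.031, with no difference between the groups.

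**The case against.** A reader might infer that the type I error does exceed 5%. The documents do not support that. It needs a rule that either outcome suffices, and no such rule appears. Study design joins prevalence and severity with a plain conjunction; if both were required, the error would fall below 5%. A success rule cannot be undefined and also have a definite inflated error rate. This objection stands, so the inflation is stated here only as conditional.

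A reader might also infer that both outcomes are to be compared between groups at 0.05. Only the score has a specified between-group model. The abstract speaks broadly of mixed-effects analysis to compare outcomes, but Statistical analysis ties the model to the score. This objection stands too, and it exposes the missing between-group test for continence.

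It can further be said that the abstract, Study design and Primary outcome measures all describe one pair, since the abstract mentions the ICIQ-SF score before it turns to secondary outcomes. That reading is fair. It reduces the conflict to a pair in three places against the score alone in the sample size calculation and Table 2, but that conflict remains.

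The power figures rest on assumed rates and an assumed equal split, and are illustrative only.

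Finally, a separate analysis plan could supply detail. But the complaint is not missing detail: the article states the primary outcome in ways that do not agree, and an analysis plan takes that outcome from the protocol.

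**Conclusion.** The point holds in this form: the primary outcome is stated inconsistently, no success rule is given, and the superiority criterion is therefore undefined.

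Type I error may exceed 5% only if either outcome may carry the claim. The excess is then small with Fisher's test (ceiling about 6.7% at an assumed 11 per arm) and reaches 9.75% for two independent tests of exact 5% size. It is absent if both outcomes are required or one is named.

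Independently of the error rate, two defects stand. The binary outcome is not what the trial is sized for: illustrative power is 17% to 32% for continence differences of 30 to 40 percentage points. And its only named test cannot show a between-group effect.

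Confidence is high on the inconsistency, the missing rule and the mismatch with the sizing. The error and power figures depend on the assumptions of two-sided tests, 1:1 allocation, and the stated ranges of correlation and continence rates. The point should be settled before recruitment.

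**What to change.** In the abstract, Study design, Primary outcome measures and Table 2, name one primary outcome: the between-group difference in ICIQ-SF score at 12 weeks, estimated from the mixed model. This matches the sample size calculation and the existing Table 2 row.

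Make continence by question 3 a key secondary outcome. Compare it between groups, for example by Fisher's exact test or a risk difference with a confidence interval, and test it only if the primary result is significant. McNemar may stay as a description of change within each arm, but not as evidence of a treatment effect.

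If the investigators prefer to keep two primary outcomes, a stated rule that both are required, or an alpha split, would also define success. With 0.025 each the total is at most 5%. Sizing would then have to cover continence as well.

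The cost is rewording and a registry update; Trials status says that recruitment had not begun. The downside is that a positive continence result alone could no longer be claimed as trial success.

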**Trial registration:**

Clinical Trials NCT04159467. Registered on 08/28/2021.

**Supplementary Information:**

The online version contains supplementary material available at 10.1186/s13063-023-07347-4.

## Introduction

Currently, the number of obese people in the world represents a growing threat to the health of populations, both in developed and developing countries [1]. According to the World Health Organization (WHO), in 2016, more than 1.9 billion adults aged 18 and over were overweight. Of these, more than 650 million adults were obese. In 2016, 39% of adults aged 18 and over (39% of men and 40% of women) were overweight. Overall, about 13% of the world’s adult population (11% of men and 15% of women) was obese in 2016 [2]. In addition to metabolic diseases, obesity can cause musculoskeletal disorders, including pelvic floor muscle disorders, the most prevalent of which is urinary incontinence (UI) [3–5].

Pelvic floor muscle training (PFMT) is considered the first-line treatment of all types of non-neurogenic urinary incontinence (UI) in women [6]. Studies have shown the positive effect of weight loss, mediated by a low-calorie diet on UI symptoms in women [7–9] but few current randomized controlled trials (RCT) have been found comparing the improvement in UI symptoms in women who have just undergone a low-calorie diet for weight loss compared to a low-calorie diet associated with PFMT.

Considering that obesity is currently among the most worrying health problems in the world, contributing to PFM dysfunctions such as UI, it is urgent to investigate in high-quality RCTs new low-risk interventions capable to optimize the results obtained only with weight loss, in the reduction of reports of UI in obese women.

## Methods

### Study design

We will conduct an assessor blind randomized, controlled, two-arm clinical trial to assess whether the combination of a low-calorie diet and PFMT will optimize the results obtained with diet therapy as a single intervention to decrease UI prevalence reports and severity in obese women (primary outcome). The secondary outcomes of this study are the impact of the protocol on PFM function, women’s self-perception of their PFM, adherence, and satisfaction with the treatment. This protocol will be reported according to the Protocol Items Standard: Recommendations for Intervention Trials checklist (SPIRIT) 2013: items recommended for a clinical trial protocol and related documents. It is a superiority trial.

### Ethic

The study was approved by the Human Research Ethics Committee of the University of São Paulo—Hospital das Clínicas of the Ribeirão Preto Medical School (HCFMRP / USP) No. 16379919.5.0000.5440 on July 9, 2019, and registered in the Clinical Trials—NCT04159467.

Any major deviation or modification of the original protocol will be reported in the Clinical Trials website and the trial records will be continuously updated as necessary.

The risks of this research basically include the possible embarrassment of the participant in answering questions related to symptoms of urinary incontinence, intestinal and vaginal pain, and embarrassment during the physical examination (vaginal palpation), in addition to feeling some discomfort during the examination and of the possible breach of confidentiality during the research.

The benefits of this research are that the participant will receive information about the anatomy of the pelvic floor, its functions, and dysfunctions, she will learn to contract this musculature and know if she is doing it correctly, contributing to prevent and/or treat its dysfunctions, in addition to also receiving a program of training for 12 weeks (if selected for group II) to strengthen the pelvic floor muscles. If you are selected for group I, you will be invited after 12 weeks to receive the same treatment as in group II.

For ethical reasons, we did not plan to prohibit any concomitant treatment. We included in the methods section our plan to monitor any concomitant treatment for pelvic floor disorders including urinary incontinence, but we expect to have homogeneous groups in relation to these variables provided by an adequate randomization and sample size.

Figure 1 shows the CONSORT (Consolidated Standards of Reporting Trials) flowchart, enrollment schedule, interventions, and study evaluations. Figure 2 shows the checklist using the SPIRIT (Standard Protocol Items: Recommendations for Interventional Trials) used in the study.

**Fig. 1 Fig1:**
[figure not shown]
Flowchart for selecting women for the randomized clinical trial, following the CONSORT

**Fig. 2 Fig2:**
[figure not shown]
Study evaluation schedule (SPIRIT). Source: According to the SPIRIT 2013 statement: Standard Protocol Item Definition for Clinical Trials

### Participants

Obese women with UI who are about to start a low-calorie diet program for weight loss will be recruited in the bariatric surgery sector at the Clinics Hospital of Ribeirão Preto Medical School (HCFMRP-USP).

### Inclusion criteria

Women over 18 years, with a body mass index (BMI) > 30 kg/m^2^; reporting stress urinary incontinence, urgent urinary incontinence, or mixed urinary incontinence in the past 4 weeks assessed by the ICIQ-SF; who are able to contract the pelvic floor muscles (assessed using vaginal palpation with a PFM contraction ≥ 2 according to the modified Oxford grading scale); and without any cognitive impairment.

### Exclusion criteria

The participants will be excluded of the study if they withdraw their consent to participate in the study or if they become pregnant.

### Criteria of discontinuing

The criteria of discontinuing the trial for a given participant include withdrawal of consent to participate and becoming pregnant during the study.

### Sample size calculation

The sample calculation was estimated considering a significance level of 5%, power of 20%, and difference of 4 points on the final score of the primary outcome, ICIQ-SF, between groups at the end of treatment [10]. The value of 4 points is equivalent to the minimum value for change in the questionnaire score. Thus, the sample will be composed of 22 participants.

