RCTs investigating a low calory diet associated to PFMT including only obese women are rare in the literature. One small RCT (*n*= 22) included both overweight and obese women and was different from our RCT compared PFMT + weight loss with a group receiving only PFMT. The study did not show the benefits of adding weight loss to PFMT. However, the limited sample size and the short duration of the protocol (8 weeks) might have importantly contributed to the lack of effect [10].

A recently published study aimed to implement and evaluate the feasibility, acceptability, and effectiveness of a 12-week group exercise and healthy eating program (ATHENA) both for overweight/obese women with UI [21]. The results indicated that ATHENA was feasible to implement, with a high percentage of women (97%) reporting improved UI symptoms and significant improvements in pelvic floor dysfunction and quality of life. No significant weight change was observed although significant improvements were found in body-food choice congruence. Different from the protocol planned for our study, the program investigated included only education about health eating that might have not is enough to provide weight loss. Nevertheless, these results are limited to provide a reliable answer related to the effectiveness of the intervention, as this is not a RCT.

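### The sample size rests on a printed power of 20% and no stated SD; read as 80%, 22 women suffice only if the ICIQ-SF SD is at most about 3.2

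*Protocol article*

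**What the plan says.** The whole justification for the trial's size is one short paragraph (Protocol article, Sample size calculation). Its inputs are a "significance level of 5%, power of 20%, and difference of 4 points on the final score of the primary outcome, ICIQ-SF, between groups". It explains the target by saying "The value of 4 points is equivalent to the minimum value for change in the questionnaire score", and concludes: "Thus, the sample will be composed of 22 participants". A reference is cited for the calculation, but no SD is given there or anywhere else in the article.

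Three other places bear on the calculation:

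- Statistical analysis: "A 95% confidence interval and 0.05 significance will be considered for all tests". The ICIQ-SF score is to be analysed with a linear mixed model with group, time and their interaction.
- Criteria of discontinuing: women may leave the trial through "withdrawal of consent to participate and becoming pregnant during the study".
- Abstract, Methods: "The participants will be randomly allocated in two groups", with no ratio stated.

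**The concern.** Power is the probability of detecting the target difference if it exists. A superiority trial planned at 20% would be expected to miss its 4-point target four times in five. Nobody is likely to have intended that; 20% is a usual value for the type II error. But the article gives no second power figure from which a reader could correct the first, and without an SD the printed 22 cannot be used to work out which was meant.

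This paragraph is what readers will turn to when the result is known. If the trial finds no significant difference, the natural reading is that pelvic floor muscle training adds nothing to diet. That reading is fair only if 22 women could have detected 4 points, and the paragraph as printed does not let anyone judge this.

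**Working it through.** **Inputs.** From the article: significance level 5%, difference 4 points on the final score, N = 22, which reads as the total. Assumed: 1:1 allocation, so 11 per arm (the article says only two groups); a two-sided test (suggested by the pairing of a 95% interval with 0.05); an unadjusted comparison of final scores, as the sample size sentence frames it; no loss. The SD is not given and is treated as unknown.

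**1. Can 22 be reproduced?** For two means, n per arm = 2 × SD² × (z₀.₉₇₅ + z_power)² / 4². With SD missing, n is undefined. The plan's figure can be neither confirmed nor refuted, so the check must run backwards: which SD makes 22 correct?

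**2. SD implied by 22, normal approximation.** Rearranged, SD = 4 × √(11/2) / (z₀.₉₇₅ + z_power), and 4 × √5.5 = 9.381.

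- Power 80%: 9.381 / (1.960 + 0.842) = 3.35.
- Power 20%: 9.381 / (1.960 − 0.842) = 8.39.

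**3. The same with the t-test.** Power comes from the noncentral t distribution with 20 degrees of freedom and noncentrality 4 / (SD × √(2/11)) = 9.381 / SD. Solving for SD:

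- Power 80%: SD = 3.185, a standardised difference of 4 / 3.185 = 1.26.
- Power 20%: SD = 8.02.

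Conversely, for SDs of 3 to 5 the literal 20% power would need only 4 to 8 women in total (normal approximation). The printed power and the printed N therefore fit together only at an SD about 2.5 times the one needed at 80% (8.02 / 3.185).

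**4. What 22 women deliver at other SDs.** The SDs are assumptions. The detectable difference at 80% power is 1.256 × SD, where 1.256 = 4 / 3.185.

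| SD | Power for 4 points, 11 per arm (t-test) | Difference detectable with 80% power |
|---|---|---|
| 3 | 84.5% | 3.8 |
| 3.2 | 79.6% | 4.0 |
| 4 | 60.7% | 5.0 |
| 5 | 43.1% | 6.3 |
| 6 | 31.9% | 7.5 |

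**5. Loss.** At SD 3.2, power is 75.3% with 10 completers per arm and 70.2% with 9 per arm.

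**6. Sensitivity to the assumptions.** A one-sided 5% test would raise the largest SD that keeps 80% power to 3.64 (t-test) or 3.77 (normal). If the mixed model's interaction works as a comparison of change scores, the relevant SD is SD × √(2(1 − r)), where r is the correlation between baseline and follow-up. At an assumed r = 0.7 the tolerable raw SD becomes 3.185 / √0.6 = 4.1; at r = 0.5 nothing changes; below 0.5 it falls. The article states no correlation.

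**The case against.** The certain error is narrow: one word, or one figure, is wrong. No miscalculation has been shown, because without an SD there is no calculation to check. The article condenses a fuller protocol and cites a source at this sentence, so the SD and any allowance for loss may be written down elsewhere; their absence alone would be missing detail and no more. The limit of 3.2 also depends on assumptions, and the mixed model might tolerate a larger SD.

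Most of this stands, and it limits what can be claimed. It does not rescue the sentence, because the power figure is printed and wrong, and nothing else in the article corrects it.

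Three stronger readings are tempting and should be resisted.

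- A reader might infer that the trial is underpowered. The article does not show this: nothing in it says whether the SD is above or below 3.2, and the 61%, 43% and 32% rest on assumed SDs.
- A reader might infer that losses were ignored. All that can be said is that no allowance is stated; 22 may or may not include one.
- A reader might take the Discussion as an admission that 22 is too few, since it says of an earlier trial of the same size that "the limited sample size and the short duration of the protocol (8 weeks) might have importantly contributed to the lack of effect". That remark also names short duration, is worded as a possibility, and concerns a trial that compared training plus weight loss with training alone. It is context and does not show that 22 is wrong here.

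**Conclusion.** The point holds in this form. The stated power of 20% is wrong as printed, probably the type II error entered as power, and 22 does not follow from the stated inputs because the SD is missing. If 80% was meant, 22 women support it only for an ICIQ-SF SD of at most about 3.2 (3.35 by normal approximation), given 11 per arm, a two-sided 5% test, an unadjusted comparison of final scores and no loss. A smaller SD gives more than 80%. A larger SD or losses give less, unless baseline and follow-up scores are correlated well enough for the mixed model to make up the difference. How far the delivered power departs from 80%, if at all, cannot be determined from the article.

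**What to change.** Rewrite the sample size paragraph to state:

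- power 80% (type II error 20%), if that was intended;
- the SD used and its source;
- whether the test is one- or two-sided;
- whether 22 already includes expected losses, and how many.

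If the SD is above about 3.2, or losses are expected on top of 22, keep 22 and restate what it delivers: either the power for 4 points or the difference detectable with 80% power. At SD 4, for example, that is 61% power, or 5.0 points. If the calculation relied on the baseline score through the mixed model, give the assumed correlation.

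The cost is a protocol correction and perhaps a less favourable stated figure; no extra women are needed. The Trials status section says that recruitment had not started, so the sponsor could instead recompute N. By the t-test that would mean 34 women at SD 4 or 52 at SD 5, before any allowance for loss.
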